### Application of the Index Test GEBS

Patients who have agreed to participate in the study will be screened with the full GEBS even if they do not show a risk of dysphagia after the first 2 steps. If any occurrence during the screening indicates dysphagia and requires the screening to be stopped and the patient to be referred to further assessment, the test result can be included in the study as “fail.” To ensure broad validation of the GEBS, the screening can be carried out by nurses, physicians, or SLPs. Investigators will be educated on the correct process and scoring of the GEBS prior to the study. To ensure intrarater reliability, 15 patients will be screened twice with the GEBS by the same investigator with a minimum of 4 hours between both events. To calculate the interrater reliability, another 15 patients will be screened twice by 2 independent investigators blinded to the respective other result of the GEBS.

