## Methods

### Test Construction

The starting point for the GEBS was a screening tool already in use at the Department of Geriatric Medicine, Christian Doppler University Hospital, in Salzburg, Austria. It has been demonstrated to be a convenient tool in clinical practice but has never been formally validated. Combined with the results of a thorough review of published evidence on possible reliable predictors for dysphagia, it was developed into a 3-step screening tool. In the first step, 6 risk factors are assessed by observation, patient reports, and chart review (Textbox 1).

Following the assessment of present risk factors and the assurance of patient vigilance, a water swallow test is administered. This consists of swallowing 10 teaspoons of clear water with breaks for voice production and 1 self-administered sip out of a cup. The test is stopped if clinical signs of aspiration such as coughing or wet voice are noted, as well as after the occurrence of one of the following items is noted: breathing difficulties, as a result of the lack of maintaining alertness, head position, or saliva control.

If the water test shows signs of dysphagia and more than one risk factor is present, the third step will be administered, which consists of swallowing a pureed bolus with a consistency of level 4 in the *International Dysphagia Diet Standardisation Initiative* (IDDSI) framework [25]. After making sure that the patient is able to stay awake and upright for 15 minutes; has control over saliva, for example, shows no sign of drooling; and is able to produce voice, several teaspoons of puree are administered with breaks for voice production. The screening must be stopped for decreased vigilance, clinical signs of aspiration, and severe drooling without compensation. Coughing, wet voice, and oral residues are considered indicators for dysphagia.

A point score will be calculated, where a score of 5 points would allow for oral nutrition and medication with pureed food of IDDSI level 4 and thickened liquids of IDDSI level 2 until further examination by an SLP; a score of <5 points would result in the instruction of *nil by mouth* until further examination with a high risk for dysphagia.

This 3-step process of determining risk factors; applying a water-swallow test; and if necessary, administrating a pureed bolus test ensures patient safety while aiming for a high specificity and sensitivity [21,26].

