### Statistical Analysis

#### Outcomes

The 2 main outcomes to be analyzed are sensitivity and specificity to detect dysphagia. These will be calculated using a 2 × 2 matrix. Further, positive and negative likelihood quotient and diagnostic odds ratio will be calculated. To assess intra- and interrater reliability, the κ coefficient will be evaluated. Additional cross-analysis with acquired data such as age; gender; medical diagnosis, including severity if assessed (National Institutes of Health Stroke Scale and Mini Mental State Examination); current diet; and dependency on activities of daily living will be considered as secondary outcomes. Calculations will be carried out using Excel (Microsoft) and SPSS (IBM Corp).

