## Discussion

### Expected Findings

The GEBS is, to our best knowledge, the first screening tool for the assessment of dysphagia in older patients to be validated against an instrumental swallowing assessment in accordance with guidelines, such as STARD and QUADAS, while taking into consideration individual predisposing factors. This is highly relevant considering the growing demand for personalized medicine in this age group. Similar to children not being small adults in regard to medication, older patients with frailty are to be considered differently for their changed muscle function, metabolism, and physical activity.

This study aims to provide geriatric facilities in the acute setting as well as in long-term care with a reliable, useful tool to screen patients for dysphagia. If the GEBS shows sufficient results to be recommended for broader use in different geriatric settings, further studies in different geriatric settings are advisable. The impact of systematic dysphagia screening with the GEBS should be evaluated by using end points such as rates of aspiration pneumonia, nutritional status, occurrence of bolus death, as well as the patient’s quality of life. Other populations such as patients with moderate to severe cognitive decline or tracheotomy tubes should also be included in further studies, to determine the validity of the GEBS in different patient groups.

Several studies have shown significant changes in the parameters mentioned above, namely pneumonia rates, nutritional status, bolus death, and quality of life, upon systematic screening for dysphagia in emergency departments or stroke units, so there is reason to expect similar effects in geriatric facilities when using a specialized geriatric dysphagia screening tool [14,16].

The screen will be used as a 2-step process in clinical use after having been validated, so the third part will only be administered if no SLP is available. If patients show a risk for dysphagia during the water swallow test and an SLP is available, the screen will be discontinued, and the patient will be referred to an SLP evaluation straight away. Especially in long-term care facilities in Austria, the presence of an SLP is not always the case. Thus, it is necessary for nursing and medical staff to be able to determine the safest method of oral intake until the swallowing function can be assessed by a specialist.

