### Conclusions

With this study, we hope to fill the gap in the health care of the older adult population by minimizing risk factors for patients and workload for caregivers at the same time. Optimized protocols and diagnostic pathways can be developed by implementing systematic, low-level screening protocols. If the results are positive in terms of high sensitivity and specificity, the GEBS will be published internationally, which might have a positive impact on workplaces and the health care of older patients.

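### Puree given after a clean water test can produce fails in the study's 2 × 2 table that the screen cannot produce in routine use

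*Protocol article*

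**What the plan says.** **How the test is run in the study.** Under Application of the Index Test GEBS, participants are "screened with the full GEBS even if they do not show a risk of dysphagia after the first 2 steps". The next sentence covers interrupted screenings: "If any occurrence during the screening indicates dysphagia and requires the screening to be stopped and the patient to be referred to further assessment", the result may be entered in the study as a fail. The rule is not limited to a particular step.

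**How the test is designed.** Test Construction makes the puree step conditional: "If the water test shows signs of dysphagia and more than one risk factor is present, the third step will be administered". At that step, "The screening must be stopped for decreased vigilance, clinical signs of aspiration, and severe drooling without compensation".

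**How the test will be used.** Expected Findings states: "The screen will be used as a 2-step process in clinical use after having been validated". Puree is then given only where no SLP is available. If an SLP is available, a patient who shows risk on the water test is referred at once.

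**What is analysed.** Under Outcomes, "The 2 main outcomes to be analyzed are sensitivity and specificity to detect dysphagia", and both come from a 2 × 2 matrix. The article does not say that this matrix is scored at the end of step 2, or that the step-2 result is analysed on its own.

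**The concern.** The index test applied in the study is broader than the one that will be used. A participant with a clean water test who shows aspiration signs on puree must be stopped, and the study rule allows that stop to be entered as a fail. The same patient on the ward gets no puree and so cannot fail on it. The accuracy figures could then include detections, and false alarms, that the deployed screen cannot generate.

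These are the two main outcomes, and the Conclusions section ties dissemination to them: "If the results are positive in terms of high sensitivity and specificity, the GEBS will be published internationally". For a screen meant to prevent aspiration pneumonia and bolus death, a missed patient is the harmful error. Sensitivity credited to puree-only detections would give users more reassurance than the 2-step screen earns.

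**Working it through.** The article states no expected sensitivity, specificity or rate of puree failure, and its 100 participants are not derived from a calculation (Results). There is no planned figure to reproduce. The check is to trace the test logic and then work out the effect per case.

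**Step 1: trace a patient with a clean water test.**

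| Setting | Puree given? | Can the patient fail on puree? |
|---|---|---|
| Study (Application of the Index Test GEBS) | Yes | Yes, if stopped |
| Routine, SLP available (Expected Findings) | No | No |
| Routine, no SLP (Expected Findings with Test Construction) | No, because water-step signs are required first | No |

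A puree-only failure is therefore possible in the study and impossible in either routine setting.

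**Step 2: trace a patient with signs on water.** In routine use this patient is referred at once if an SLP is available. If none is available and more than one risk factor is present, puree is given. A score of 5 then allows a modified diet, and a lower score means nothing by mouth. Both apply only until an SLP examination. Puree thus changes the interim diet but does not cancel the need for an SLP examination, so the water-step failure is the natural routine fail.

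**Step 3: write the study figures in terms of the 2-step figures.** Let
- P and N be the numbers FEES-positive and FEES-negative;
- a and b be the puree-only failures among them;
- c and d be the FEES-positive and FEES-negative water-step failures who tolerate puree and are then scored as passes.

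Sensitivity (study) = sensitivity (2-step) + (a − c)/P

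Specificity (study) = specificity (2-step) − (b − d)/N

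If water-step failures always remain fails, c = d = 0. The study figures can then only be higher for sensitivity and lower for specificity. If c or d is above zero, the direction is open.

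**Step 4: effect of one case, with c = d = 0 and 100 participants.** The number FEES-positive is an assumption. The Abstract gives prevalences as high as 44% in acute geriatric care and 80% in long-term care. The value 62 is their mean, (44 + 80)/2, with equal site sizes assumed. The value 30 is an assumed low case.

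| FEES-positive P | FEES-negative N | One FEES-positive puree-only failure: sensitivity | One FEES-negative puree-only failure: specificity |
|---|---|---|---|
| 30 | 70 | +1/30 = +3.3 points | −1/70 = −1.4 points |
| 44 | 56 | +1/44 = +2.3 points | −1/56 = −1.8 points |
| 62 | 38 | +1/62 = +1.6 points | −1/38 = −2.6 points |

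The total shift is a or b times the per-case figure. The documents give neither a nor b.

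**The case against.** **The fail rule is permissive.** The article says that an interrupted screening may be included as a fail. This can be read as a way of keeping incomplete screenings in the data, not as the definition of a positive test, and a full protocol may set a cut-off. That stands: a reader might infer that every puree stop will be counted, and the text does not go so far. It is, however, the only classification rule shown for a stopped screening. It covers puree stops without exception, and it conflicts with a use that the article also states. The point does not depend on a missing detail.

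**The direction of bias is not guaranteed.** A reader might infer that sensitivity is bound to be overstated. Test Construction does not say outright that a participant who shows signs on water and then tolerates puree remains a fail. If such participants were scored as passes, study sensitivity could fall below that of the 2-step screen. This objection stands, so the direction is stated only under that condition.

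**The GEBS is a 3-step tool, and step 3 survives where no SLP is available.** Validating the full tool is coherent, and long-term care is one of the two sites. But even there puree follows only a water test with signs, so this does not bring puree-only failures into routine use.

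**Puree-only failures may be rare.** The tool itself uses puree and thickened liquids as the interim diet for some patients who show signs on water, which suggests that it treats them as safer than water. This is fair. Nothing in the documents says that such failures are common, and no total effect can be claimed.

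**Conclusion.** The point holds as a mismatch between the test as scored in the study and the test as it will be used. As written, puree-only failures can enter the main 2 × 2 table, and the reported sensitivity and specificity would then not be those of the routine screen.

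Provided that water-step failures stay fails whatever happens on puree, the extra fails raise sensitivity or lower specificity and can do nothing else. With 44 of 100 FEES-positive (assumed), each case moves sensitivity by 2.3 points or specificity by 1.8. Across 30 to 62 FEES-positive, the ranges are 3.3 to 1.6 and 1.4 to 2.6 points. The number of cases, and so the total shift, is unknown and may be small.

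One further reading goes too far. A reader might infer that a patient missed by the 2-step screen would be put on a normal diet, but the article gives diet instructions only for a score of 5 and for lower scores. It says nothing on diet after a clean water test.

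**What to change.** Keep giving all three steps, since the puree data are useful, and record the result after step 2 separately. Score the main 2 × 2 table by the routine algorithm:

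- Any aspiration sign or stop at the water step is a fail, whatever the puree result.
- Puree results after a clean water test are not counted in this table. Participants who show signs on puree are still referred for safety.

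Report the full 3-step 2 × 2 table as a secondary result, with the number of puree-only failures by FEES result. If the full version proves clearly better, change the routine algorithm before recommending the screen.

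The cost is a sentence in the analysis section and, if the form does not already record each step, one extra field. No participants, visits or procedures are added. The small downside is that the main table loses the puree-only detections, which the secondary table still shows.

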### Application of the Reference Test FEES

Within 7 days of the first assessment using the GEBS, the reference test FEES will be carried out to verify the results. This time frame limits possible changes in the patients’ medical status between the 2 investigations of their swallowing function. The FEES is considered the gold standard, objective diagnostic tool for dysphagia in older patients and is considered particularly safe and only mildly uncomfortable for the majority of patients. Reported adverse events are epistaxis, bradycardia or tachycardia, lowering of blood pressure, and changes in heart rate, all of which are rare with a reported occurrence of less than 4%. None of these reported events that were directly caused by undergoing the FEES have ever been reported as leading to permanent damage; all are self-limited and of a very short duration [30,31]. The results of the FEES will be reported using the *penetration-aspiration scale* developed by Rosenbek et al [32] in 1996; it is an internationally established 8-point scale to rate the severity of dysphagia. To limit uncomfortable sensation for the patients while the endoscope is passed through the nasal cavities, a local anesthetic can be used, which does not affect the swallowing function if used correctly [33,34]. The FEES investigators will be blinded to the results of the GEBS.

### Statistical Analysis

#### Outcomes

The 2 main outcomes to be analyzed are sensitivity and specificity to detect dysphagia. These will be calculated using a 2 × 2 matrix. Further, positive and negative likelihood quotient and diagnostic odds ratio will be calculated. To assess intra- and interrater reliability, the κ coefficient will be evaluated. Additional cross-analysis with acquired data such as age; gender; medical diagnosis, including severity if assessed (National Institutes of Health Stroke Scale and Mini Mental State Examination); current diet; and dependency on activities of daily living will be considered as secondary outcomes. Calculations will be carried out using Excel (Microsoft) and SPSS (IBM Corp).

#### Data Management

Acquired data for the study will be managed and pseudonymized with the keys being stored at the recruiting institution and not available to the study coordinator. Data will be stored using Excel (Microsoft) following the legal requirements of the Austrian government.

### Ethics Approval

Ethics approval has been obtained for both study centers. First, the ethics committee of the City of Vienna approved the study (EK 21-212-1021) in March 2022. The ethics committee of the Province of Salzburg gave approval (EK-Nr. 1040/2022) in June 2022. Required changes were the complete exclusion of patients who are not able to give their informed consent due to cognitive diseases as well as minor clarifications in the patients’ information document. The study was registered with the ISCRTN registry (11581931) in March 2021.

## Results

Recruitment started in October 2022 and will end in April 2024. A planned total of 100 participants will be aimed for. Since there have not been prior studies using the GEBS, no expected effect can be used to calculate a power analysis. Regarding previously published, internationally established screening tools, a case number of 100 patients was decided on. However, if, by the end of the study period, fewer results have been obtained, recruitment will not be extended further. Data publication is planned for early 2025, following the end of the collection period.

## Discussion

### Expected Findings

The GEBS is, to our best knowledge, the first screening tool for the assessment of dysphagia in older patients to be validated against an instrumental swallowing assessment in accordance with guidelines, such as STARD and QUADAS, while taking into consideration individual predisposing factors. This is highly relevant considering the growing demand for personalized medicine in this age group. Similar to children not being small adults in regard to medication, older patients with frailty are to be considered differently for their changed muscle function, metabolism, and physical activity.

This study aims to provide geriatric facilities in the acute setting as well as in long-term care with a reliable, useful tool to screen patients for dysphagia. If the GEBS shows sufficient results to be recommended for broader use in different geriatric settings, further studies in different geriatric settings are advisable. The impact of systematic dysphagia screening with the GEBS should be evaluated by using end points such as rates of aspiration pneumonia, nutritional status, occurrence of bolus death, as well as the patient’s quality of life. Other populations such as patients with moderate to severe cognitive decline or tracheotomy tubes should also be included in further studies, to determine the validity of the GEBS in different patient groups.

Several studies have shown significant changes in the parameters mentioned above, namely pneumonia rates, nutritional status, bolus death, and quality of life, upon systematic screening for dysphagia in emergency departments or stroke units, so there is reason to expect similar effects in geriatric facilities when using a specialized geriatric dysphagia screening tool [14,16].

The screen will be used as a 2-step process in clinical use after having been validated, so the third part will only be administered if no SLP is available. If patients show a risk for dysphagia during the water swallow test and an SLP is available, the screen will be discontinued, and the patient will be referred to an SLP evaluation straight away. Especially in long-term care facilities in Austria, the presence of an SLP is not always the case. Thus, it is necessary for nursing and medical staff to be able to determine the safest method of oral intake until the swallowing function can be assessed by a specialist.

To spare patients unnecessary diagnostic processes and restrictions in their oral intake, specific diagnostic pathways and case-specific treatment need to be administered. A fast and safe way to ensure oral intake and medication in older patients can assist doctors and nursing staff upon the admission of new patients and streamlines SLP personnel resources.

### Limitations

A limiting factor is the exclusion of patients with moderate to severe cognitive diseases. This is a growing population that is highly susceptible to developing dysphagia. This might be a future project after a first successful validation of the GEBS.

### Conclusions

With this study, we hope to fill the gap in the health care of the older adult population by minimizing risk factors for patients and workload for caregivers at the same time. Optimized protocols and diagnostic pathways can be developed by implementing systematic, low-level screening protocols. If the results are positive in terms of high sensitivity and specificity, the GEBS will be published internationally, which might have a positive impact on workplaces and the health care of older patients.

## Abbreviations

FEES: fiberoptic endoscopic evaluation of swallowing
GEBS: geriatric bedside swallowing screen
IDDSI: International Dysphagia Diet Standardisation Initiative
SLP: speech language pathology (or pathologist)
STARD: Standards for Reporting Diagnostic Accuracy
QUADAS: Quality Assessment of Diagnostic Accuracy Studies
